### Randomization and blinding

After ensuring study eligibility and completing baseline assessments, the participants will be randomly assigned to either ULAE plus general exercise group or general exercise alone (control) group. Randomization will be performed by an independent person (a record officer) at each study site using computer-generated random numbers. To ensure allocation concealment, sequentially numbered, opaque, sealed envelopes will be prepared in accordance with the generated random sequence. Upon the availability of an eligible participant at the scheduled appointment, the next envelope will be opened to determine the intervention group to which the participant is allocated. Outcome assessors will be blinded to group allocation. However, owing to the nature of the study interventions, blinding of the physiotherapists administering treatment will not be possible. Unbinding will only be permissible in cases where a participant experiences a serious adverse event or after the study’s completion.

### Explanation for the choice of comparators

General exercises are typically prescribed by physiotherapists for individuals with SCI, as they enhance cardiovascular health, muscle strength, and flexibility; prevents secondary complications; improve mood and mental well-being; and enhance overall QOL. As such general exercise may be considered a standard of care. This study intends to determine the effects of adding ULAE to general exercise (i.e., the experimental intervention) compared to general exercise alone (i.e., active control intervention). The use of an active control group will help to minimize the likelihood of attributing improvements observed in the experimental group solely to a placebo effect.

### Study interventions

All the study interventions will be administered under the supervision of physiotherapists holding a postgraduate degree in musculoskeletal physiotherapy. They will receive training on the study intervention protocols prior to the commencement of the study by the primary researcher. Both groups will receive general exercise, while participants in the ULAE group will additionally perform arm ergometer and overhead pulley exercises. All interventions will be administered three times per week for 8 weeks.

### Upper-limb aerobic exercise (ULAE)

A Bike Portable Under-Desk Arm Leg Foot Exerciser Stationary (TDC T-C CA, Japan) with an adjustable multi-level resistance system will be used to perform ULAE, based on the recommendations of the American College of Sports Medicine (ACSM) [19]. The exercise protocol will consist of three phases: warm-up, exercise, and cool-down. For both the warm-up and cool-down phase, participant will pedal the ergometer for 5 minutes without resistance. The exercise phase will be tailored according to each participant’s ability and strength, and will involve 20 minutes of pedaling aiming for light to moderate intensity. The target heart rate will be maintained between 50–70% of estimated maximum heart rate (220 – age). Participants will be encouraged to maintain a pedaling rate between 50 and 60 revolutions per minute (RPM). Resistance will be gradually increased over the weeks by adjusting the tension knob on the exerciser. The heart rate of the participants will be monitored using a digital heart rate monitor to be worn on their wrists. Following the arm ergometer exercise and adequate rest, participants will perform reciprocal or overhead pulley exercise using an 85-inch reciprocal pulley (Samvsine, USA) for 10 minutes. The exercise sessions will be conducted three times per week on non-consecutive days for 8 weeks.

### General exercise

The general exercise program will be tailored to the patient’s neurological level and abilities, and will include passive, active-assisted, and free active range of motion (ROM) exercises, as well as stretching and strengthening exercises for the upper and lower body [15]. These exercises will be performed in various positions including sitting, prone, supine, quadruped, kneeling, and standing. ROM exercises will utilize the reciprocal pulley while strengthening exercises will involve the use of sandbags and dumbbells of varying weights. The exercise will be targeted at key muscles of body (i.e., deltoids, triceps, biceps, pectoralis, wrist flexors, wrist extensors, quadriceps, hamstrings, and gastrocnemius). Exercises will be performed at moderate intensity, which is considered safe for SCI people, as recommended by the ACSM [19]. Each exercise will be held for 10–15 seconds, repeated 10 times , with a 5-second rest between repetitions and a 60-second rest between different exercise types. The exercise sessions will be conducted three times per week for 8 weeks.

### Strategies to improve adherence to interventions

To enhance adherence to the interventions, participants will be thoroughly briefed during the consent process on the importance of attending all treatment sessions and completing outcome assessments after intervention and at the 14 weeks follow-up. Additionally, participants will receive regular follow-up reminders via phone calls to encourage consistent participation.

### Relevant concomitant care permitted or prohibited during trial

Relevant concomitant care, such as medications, will be permitted during the trial, However, any other experimental treatments that could confound the effects of the studied interventions will be prohibited.

### Adverse events

All necessary precautions will be taken to prevent the occurrence of any adverse events. Participants will be fully informed of the potential for both serious and non-serious adverse events prior to the commencement of the study interventions. In the event of a serious adverse event (e.g., injuries, persistent excruciating pain, decrease in spine ROM) at any point during the trial, the primary researcher will be immediately notified. The participant may be withdrawn from the study, and appropriate medical care will be sought from a physician. Additionally, reports of serious adverse events will be submitted to the Health Research Ethics Committees of NOHD, AKTH, and Kano State Ministry of Health, Nigeria. Non-serious adverse events that may occur include physical exertion, muscle soreness, dizziness, and exacerbation of muscle or joint pain. These will be monitored and managed appropriately throughout the trial.

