### Informed consent

Informed consent will be obtained by the physiotherapist responsible for eligibility assessment after providing participants with a detailed explanation of the study, including its benefits and procedures. Participants will be informed that they have the right to withdraw from the study at any time without any prejudice or negative consequences.

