### Sample size calculation

To our knowledge, no previous study has evaluated the effects of ULAE plus general exercise program compared to general exercise alone among SCI patients, using the RPP (product of SBP and HR) as an outcome. However, since the minimal clinically important difference (MCID) for total Spinal Cord Independence Measure III (SCIM III) has been reported to be 10.0 points [17], this study was powered to detect a minimum difference of 10% points between the ULEA group and control group (assuming a standard deviation [SD] of 12.0, based on the study by Akkurt et al. [15]. Using the following parameters— F-test, repeated measures, between-subjects analysis of variance (ANOVA); alpha (*α*) level of 0.05; power of 0.80; effect size of 0.40 when accounting for 3 repeated measures; and correlation among repeated measures of 0.5— a total of 36 participants was required. Accounting for a potential dropout rate of 30% (n = 10), the final sample size was determined to be 46 participants. Calculations were performed using G Power 3.1.9.2 software [18].

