### Data collection tools and outcome measures

Outcome assessments will be conducted prior to randomization by a physiotherapist who will not take part in other aspects of the study (Fig 2). To enhance the consistency of self-report questionnaires, outcome assessors at each of the study centers will be trained by the primary researcher in interviewer-administered questionnaire techniques prior to data collection. Assessments will be performed at baseline (pre-intervention), 8 weeks post-intervention, and 14 weeks follow-up.

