### Data analysis

All statistical analyses will be conducted on IBM SPSS Statistics version 24.0 (IBM Co., Armonk, NY, USA), with a significance level at 0.05.

Descriptive statistics of means and standard deviations will be used to summarize continuous variables, while frequencies and percentages will be used for categorical variables. Data distribution will be assessed statistically using the Kolmogorov–Smirnov and Shapiro–Wilk tests, and visually through histograms, Q-Q plots, and box plots. Baseline comparisons of continuous variables between groups will be conducted using independent *t-*test while the chi-square (χ²) test will be used for categorical variables. For normally distributed data, a mixed model analysis of variance (ANOVA) with a 2 x 3 design (treatment group [ULAE group versus control group] x time [baseline, 8-week post-intervention, and 14-week follow-up]) will be employed to evaluate treatment effectiveness. The treatment group (between-subject factor) will be treated as a fixed effect, while time (within-subject factor) will be treated as a random effect. For non-normally distributed data, the Mann–Whitney *U* test will be used. Potential confounding variables, such as sex, education level, BMI, duration of injury, and type of injury will be adjusted for in the analysis. The intention to treat (ITT) principle will be applied, with all randomized participants included in the analysis according to their originally assigned treatment groups, regardless of whether they completed treatment.

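### The adverse-event rule lets a participant be withdrawn from the study, with no option of stopping only the exercise, so obtainable week 8 and week 14 outcomes may be lost

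*Protocol article*

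**What the plan says.** All references are to the protocol article.

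- **Adverse events.** Serious events are introduced with "In the event of a serious adverse event (e.g., injuries, persistent excruciating pain, decrease in spine ROM) at any point during the trial", and the primary researcher is to be notified at once. The next sentence gives the consequence: "The participant may be withdrawn from the study, and appropriate medical care will be sought from a physician". No other consequence for participation is named.
- **Informed consent.** A participant's own choice to leave is described in much the same terms: "Participants will be informed that they have the right to withdraw from the study at any time without any prejudice or negative consequences".
- **Study interventions.** "All interventions will be administered three times per week for 8 weeks".
- **Data collection tools and outcome measures.** "Assessments will be performed at baseline (pre-intervention), 8 weeks post-intervention, and 14 weeks follow-up".
- **Strategies to improve adherence to interventions.** Participants are briefed on attending sessions and on "completing outcome assessments after intervention and at the 14 weeks follow-up", and they receive telephone reminders.
- **Data analysis.** Intention to treat applies, "with all randomized participants included in the analysis according to their originally assigned treatment groups, regardless of whether they completed treatment".
- **Sample size calculation.** 36 participants are required and 10 are added for dropout, so "the final sample size was determined to be 46 participants".

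**The concern.** Stopping a treatment and leaving a trial are different events. An intention-to-treat comparison needs outcomes from people who stopped treatment, so a safety rule should act on the treatment and leave measurement alone as far as the participant agrees. Here the only step named acts on the study as a whole. No criterion says when to use it, so sites may use it differently.

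The example events (injury, severe persistent pain, reduced spinal movement) could plausibly lower functional independence, which is a primary outcome. Outcomes lost this way may therefore be related to the values they would have taken. Sensitivity analyses can bound the effect of missing values but cannot replace a measurement that was available and not taken.

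**Working it through.** **1. Reading the sections together.**

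| Question | What the article states |
|---|---|
| What may follow a serious adverse event? | Withdrawal from the study, at discretion, plus medical care (Adverse events) |
| Is stopping only the exercise named as an option? | No |
| Who is to be analysed? | Everyone randomized, whether or not treatment was completed (Data analysis) |
| Is a person withdrawn after an event still invited to assessments? | Not stated in Adverse events, Strategies to improve adherence, Data collection tools or Data analysis |

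The Data analysis section settles who belongs in the analysis set. It does not settle whether outcomes are still collected after withdrawal. An event before week 8 that leads to withdrawal can cost both post-baseline assessments.

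**2. The plan's own figure, for scale.** Inputs from the Sample size calculation section: f = 0.40, m = 3 measures, correlation 0.5, alpha 0.05, power 0.80. For the between-groups test in a repeated-measures design, the noncentrality is f² × N × m / (1 + (m − 1) × 0.5), with 1 and N − 2 degrees of freedom.

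- N = 36: 0.16 × 36 × 3 / 2 = 8.64, power 0.815.
- N = 34: 0.16 × 34 × 3 / 2 = 8.16, power 0.791.
- N = 46: 0.16 × 46 × 3 / 2 = 11.04, power 0.901.

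The stated 36 is reproduced as the smallest even total with power of at least 0.80. The allowance of 10 is 10/46 = 22% of those enrolled. Withdrawals after adverse events draw on that allowance, and a total loss of 12 would leave 34 and take power just under 0.80. This check shows how much room there is. It does not test the adverse-event wording.

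**3. Illustration of a shift in the comparison.** Assumptions that are not in the document: equal allocation (46/2 = 23 per arm), and withdrawn participants who would have scored D points below the rest of their arm on SCIM-III. Leaving w of 23 out of an arm raises its observed mean by D × w / 23, so the between-arm comparison shifts by D × (difference in withdrawals) / 23.

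| D (assumed) | Difference in withdrawals | Shift in SCIM-III points |
|---|---|---|
| 10 | 0 | 0 |
| 10 | 1 | 10/23 = 0.43 |
| 10 | 2 (for example 3 versus 1) | 20/23 = 0.87 |
| 5 | 1 | 5/23 = 0.22 |
| 20 | 1 | 20/23 = 0.87 |

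Against the plan's target of 10 points and its SD of 12.0, a shift of 0.43 is 4.3% of the target and 0.43/12.0 = 0.036 SD.

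**The case against.** The case on the other side has real weight.

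- **It is an article, and the full protocol is not shown.** Procedures for follow-up after discontinuation are often left to the full document, and their absence here is no finding. That holds for detail. It does not cover a sentence that the article does state and that names study withdrawal as the step.
- **The sentence is permissive.** It neither requires withdrawal nor says that assessments stop. A reader might infer that every serious event ends follow-up; the text does not support that.
- **Other sections lean towards continued assessment.** The briefing, the reminders and the assessment schedule are not limited to people still exercising, and the Data analysis section recognises that treatment may not be completed. A reader might infer that the adverse-event rule contradicts intention to treat. It does not: one sentence governs participation, the other the analysis set. Even so, none of these sections says that someone already withdrawn is invited back.
- **Timing.** A reader might infer a rule of withdrawal running through weeks 8 to 14, when no trial exercise remains to be stopped. The words on timing belong to the sentence about notifying the primary researcher, and the withdrawal sentence carries none. Carry-over is only a possible reading. Nor is the share of calendar weeks after exercise ends a measure of risk.
- **The matching consent wording** shows that the term is not reserved for a lesser step, but everyday phrasing in a consent paragraph does not fix its operational meaning.

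**Conclusion.** The point stands as a modest one. The article lets a participant with a serious adverse event be withdrawn from the study, at discretion and without a criterion, and names no step that ends the exercise alone. Outcomes at weeks 8 and 14 that could have been collected may be lost, which works against the aim of analysing everyone randomized.

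Its size is unknown. No serious event rate is given, so the number affected cannot be derived and may be very small. The illustrative shifts of 0 to 0.87 points rest wholly on assumed deficits, assumed imbalances and equal allocation. A reader might infer that the result would favour one arm, since only one arm does the added aerobic exercise. Nothing in the document shows that either arm would lose more participants, so no direction of bias is claimed. What justifies a change is that the loss is avoidable and the remedy is cheap.

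**What to change.** Reword the consequence in the Adverse events section along these lines: after a serious adverse event the exercise sessions may be stopped on medical advice and care arranged. The participant remains in the study and is invited to the 8-week and 14-week assessments already scheduled, unless they withdraw consent for data collection. Medical care and the right to leave are unchanged, and no visit or measurement is added.

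The cost is one sentence, a site briefing, some effort to recall people who have stopped exercising, and notification of the amendment to the ethics committees and the registry, as the Ethical consideration section requires. The benefit is limited by timing. The Trial status section puts the opening of recruitment at 1 February 2023 and expects final follow-up by 30 December 2024, so the change helps only participants who have not yet reached week 14.

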### Baseline data collection

Sociodemographic and clinical characteristics, including age, sex, marital status, education level, occupational status, height, weight, body mass index (BMI), duration of injury, type of injury, level of affectation, and presence of comorbidities will be collected. American Spinal Injury Association (ASIA) Impairment Scale will be used to classify the level of injury [20]. Each participant will be assigned a unique ID for anonymity and tracking purposes.

### Data collection tools and outcome measures

Outcome assessments will be conducted prior to randomization by a physiotherapist who will not take part in other aspects of the study (Fig 2). To enhance the consistency of self-report questionnaires, outcome assessors at each of the study centers will be trained by the primary researcher in interviewer-administered questionnaire techniques prior to data collection. Assessments will be performed at baseline (pre-intervention), 8 weeks post-intervention, and 14 weeks follow-up.

**Fig 2 pone.0321932.g002:**
[figure not shown]
Schedule of enrollment, interventions, and assessments.

### Primary outcome measures

The primary outcomes are the RPP to be assessed using a digital BP monitor and functional disability to be assessed using the SCIM-III.

**Rate pressure product (RPP):** This is calculated as the product of SBP and heart rate (HR). It serves as a measure of cardiac workload, reflecting the stress put on the cardiac muscle based on the number of beats per minute. RPP is a clinically validated tool for assessing cardiac workload and cardiovascular health [21]. To measure BP (SBP and DBP) and HR, a digital BP monitor (Omron M2, HEM-7143-E) will be used. The participant will be seated comfortably with their back and arm fully supported on a flat surface at heart level. The cuff of the sphygmomanometer will be placed over the bare upper arm with the artery mark positioned directly over the brachial artery. By pressing the start button, the BP (SBP and DBP in millimeters of mercury [mmHg]) and HR in beat per minute (bpm) will be displayed on the large digital panel and recorded. The digital BP monitor is preferred because minimizes discomfort from cuff over-inflation and provides quick measurements. Intra-rater reliability of the BP measurements will be reported in the main trial.**Spinal Cord Independence Measure version III (SCIM-III):** This will be used to assess the functional independence of the participants. It consists of 19 tasks organized into three subscales: self-care, respiration and sphincter management, and mobility. Each subscale is scored on a 100-point scale (self-care: 0–20; respiration and sphincter management: 0–40; mobility: 0–40), with 0 indicating total dependence and 100 indicating complete independence [22]. The SCI-III has demonstrated adequate reliability (Kappa score = 0.696–0.983; Cronbach’s alpha = 0.923) and validity [23].

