## Introduction

Spinal cord injury (SCI) is a devastating injury accompanied by physical, psychosocial, and economic problems, as well as significant personal and social repercussions [1]. It is often associated with distinct diverse secondary complications including acute complications such as bradyarrhythmias, hypotension, impaired temperature, pain, spasticity, and autonomic dysreflexia [2] and chronic complications such as cardiopulmonary, intestinal, urinary bladder, and sexual disorders [3]. Long-term secondary complications can increase morbidity and negatively impact functional independence, community participation, and quality of life (QOL) [3]. Additionally, individuals with SCI, depending on their type of injury, often experience reduced physical activity levels, which is considered antecedent to development of various complications [4]. Individuals with SCI are approximately 40% less physically active compared to able-bodied counterparts [5].

A major complication linked to physical inactivity in individuals with SCI is the increased prevalence and earlier onset of cardiovascular disease (CVD) [6]. Research suggests that individuals with SCI, particularly those with cervical and thoracic levels of injury, often struggle with unstable blood pressure (BP), leading to persistent hypotension and episodes of uncontrolled hypertension [7].

Following SCI, there is an immediate disruption in connections between supraspinal structures and sympathetic preganglionic neurons. This leads to instability, causing spinal circuits to solely regulate sympathetic activity, which impacts BP control. Acute SCI, particularly at the cervical level, often results in severe hypotension and persistent bradycardia, contributing to neurogenic shock. However, the recognition and management of these cardiovascular dysfunctions following SCI pose significant clinical challenges. Moreover, CVD in both the acute and chronic stages of SCI is among the most common causes of mortality in this population [8].

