### Inclusion criteria

To be eligible for the study, participants must meet the following criteria:

Received medical clearance from their physicians confirming they are fit to participate in exercise.Male or female aged 18–65 years old.Diagnosed with traumatic SCI between the 7^th^ cervical (C7) and 5^th^ lumbar (L5) vertebrae, with a minimum of 3 months post-injury.Upper limb muscle power of at least 3, as assessed by gross muscle power testing, to be able to propel an arm crank ergometer.Willing to participate and having provided signed informed consent.

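### As written, RPP and BP come from one press-and-record reading with no averaging, rest or interval since exercise, which allows avoidable noise and leaves an acute exercise effect at week 8 possible

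*Protocol article*

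**What the plan says.** The protocol article names RPP (SBP multiplied by heart rate) as one of two primary outcomes, and SBP and DBP as secondary outcomes. All three come from the same device reading.

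The Primary outcome measures section is specific about that reading. It gives the monitor model, the posture ("The participant will be seated comfortably with their back and arm fully supported on a flat surface at heart level"), the bare arm and the cuff position. The start button is then pressed and the result, including "HR in beat per minute (bpm) will be displayed on the large digital panel and recorded", is taken from the display. It states no number of readings, averaging rule, rest period or interval since exercise. It does add that "Intra-rater reliability of the BP measurements will be reported in the main trial".

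Other sections bear on the timing and the population:
- Data collection tools and outcome measures puts assessments at baseline, 8 weeks and 14 weeks.
- Randomization and blinding puts the baseline assessment before allocation.
- Study interventions gives both arms three sessions a week for 8 weeks. For the ULAE component: "The exercise sessions will be conducted three times per week on non-consecutive days for 8 weeks".
- The Introduction says that people with SCI, particularly at cervical and thoracic levels, "often struggle with unstable blood pressure (BP), leading to persistent hypotension and episodes of uncontrolled hypertension". The Inclusion criteria admit injuries from C7 to L5.

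**The concern.** Two separate issues arise from the same procedure.

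**Precision.** RPP is a product, so reading error in SBP and in heart rate both enter it. A single reading carries that error in full, in a population whose blood pressure the protocol itself describes as often unstable. The trial plans 46 participants and was sized on SCIM III, not RPP, so it has little precision to spare on this outcome.

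**Possible carry-over at week 8.** The week-8 visit falls as the sessions end, and nothing separates the reading from a session. Baseline precedes every session, so adjusting for it cannot remove an acute post-exercise effect at week 8. The arms also receive different exercise: ULAE adds arm ergometry and a pulley block to the general exercise. If readings were taken soon after sessions, the week-8 contrast could combine the 8-week training effect with a short-lived effect that differs by arm.

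**Working it through.** **The plan's own figures.** The protocol gives no SD, correlation or target difference for RPP. Its pre-dropout total of 36 does reproduce: a between-factors repeated-measures F-test with f = 0.40, 3 measures, correlation 0.5 and alpha 0.05 gives power 0.815 at N = 36 and 0.791 at N = 34. That calculation concerns SCIM III and says nothing about RPP precision, so what follows rests on stated assumptions.

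**Assumed inputs.**
- Mean SBP 120 mmHg and heart rate 75 bpm, so RPP = 120 × 75 = 9,000.
- Between-person SD of true RPP 1,800, so variance 3.24M.
- Single-reading error SD from 4 mmHg with 3 bpm (low) to 8 mmHg with 5 bpm (high).
- Correlation between true values at two visits: 0.5 (the only correlation in the protocol, given for SCIM III) or 0.8.
- Independent errors between readings within a visit.

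**Reading error of RPP** (delta method): variance = (75 × SD of SBP)² + (120 × SD of HR)².
- Low: 300² + 360² = 219,600, SD about 469. Mean of three: 219,600/3 = 73,200, SD about 271.
- High: 600² + 600² = 720,000, SD about 849. Mean of three: 240,000, SD about 490.

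**Residual variance after baseline adjustment** = V − C²/V, where V = 3.24M + error variance and C = correlation × 3.24M.

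| Correlation | Error | One reading | Mean of three | Reduction | Equivalent extra participants |
|---|---|---|---|---|---|
| 0.8 | low | 1.518M | 1.285M | 15% | 18% |
| 0.8 | high | 2.263M | 1.549M | 32% | 46% |
| 0.5 | low | 2.701M | 2.521M | 7% | 7% |
| 0.5 | high | 3.297M | 2.726M | 17% | 21% |

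The last column is the ratio of the two residual variances minus 1.

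**Cross-check without a correlation.** If a share w of single-reading variance is within-visit noise, averaging three leaves (1 − w) + w/3. For w from 0.1 to 0.5 this is 0.933 to 0.667, a reduction of 7% to 33%.

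**Carry-over, for scale only.**
- At 120 mmHg and 75 bpm, an acute change of −5 mmHg gives 115 × 75 − 9,000 = −375 (−4%). An acute change of +5 bpm gives 120 × 80 − 9,000 = +600 (+7%).
- Starting from 120 mmHg and 80 bpm (RPP 9,600), shifts of 0 to −8 mmHg and 0 to +8 bpm move RPP by between −6.7% and +10.0%.

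The sign is therefore undetermined. These are shifts in one person's reading. The bias in the contrast would be only the difference between arms, which cannot be estimated from the protocol.

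**Week 14.** This visit is 14 − 8 = 6 weeks after the sessions end, so acute carry-over does not reach it.

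**The case against.** The strongest reply is that the words for a single reading never appear. The promised intra-rater reliability needs repeat readings in at least some participants, and an article can leave replicates, rest and timing to the full protocol. The schedule figure is also not visible. Part of this stands: one reading is an inference. However, the section goes down to cuff placement and the button press, and nothing says that any repeat readings enter the outcome. A site following the text would take one.

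A reader might infer that the week-8 RPP comparison is biased by exercise carry-over. The protocol does not support that. No section places the assessment after a session, and even a session-day visit matters only if the reading follows the exercise. The control arm also trains three times a week at moderate intensity and uses the pulley, so the shifts above cannot be assigned to the ULAE arm alone.

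A reader might also infer that reading noise distorts the treatment effect. It is equal in expectation between arms and costs only precision.

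Three further limits stand:
- The exclusion of serious or unstable cardiovascular disorders, with the required medical clearance, removes some of the instability described in the Introduction.
- Back-to-back readings do not remove hour-to-hour or day-to-day lability.
- The variance calculation assumes baseline adjustment, whereas Data analysis specifies a 2 × 3 mixed ANOVA with baseline as a time level.

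**Conclusion.** The point holds as a cheap improvement to a stated procedure. As written, RPP, SBP and DBP rest on one press-and-record reading with no averaging, rest or separation from exercise. The firm consequence is avoidable loss of precision. Averaging three readings would lower residual variance by about 7–17% at a visit correlation of 0.5, or 15–32% at 0.8. These figures depend on the assumed RPP mean, SD and reading errors, and on independent errors between successive readings.

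An arm-dependent acute effect at week 8 is possible under the text and would not be removed by the baseline. It is not shown to occur, and neither its size nor its direction can be derived. The week-14 comparison is not affected.

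**What to change.** Amend the Primary outcome measures section so that:
- RPP, SBP and DBP are each the mean of repeat readings (for example three, one minute apart, on the same device) after a fixed period of seated rest.
- RPP is computed for each reading and then averaged, so that each SBP stays paired with its own heart rate.
- The week-8 measurement is taken before any exercise that day, preferably on a non-session day, identically in both arms.

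Apply this to visits still to come. The Trial status section anticipated final follow-up by 30 December 2024, so few may remain. For completed visits, keep every reading in the primary intention-to-treat analysis. Record from attendance logs whether a session took place on the assessment day, and repeat the RPP analysis without those readings. That repeat is a sensitivity analysis only, because it selects on something that happens after randomization.

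The cost is a few extra minutes per visit with the device already in use, a line on the data form, and possibly an attendance on a non-session day. If some visits are already done, the measurement procedure changes part-way. The report should say so and state which visits used which procedure.
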